## Methods

### Study design

Veterans experiencing or at risk for food insecurity, diagnosed with a cardiometabolic diet sensitive condition including hypertension, obesity, and/or diabetes, and a comparison group of similar Veterans will be enrolled in VA FCPRx to estimate the effect of produce prescription on clinical measures, healthcare utilization, and self-reported behavior and well-being.

Primary outcomes: Clinical measures, including body mass index (BMI), blood pressure, and metabolic control (HbA1c) derived from the VA EHR.

Secondary outcomes: Healthcare utilization, including primary care visits, pharmacy utilization, inpatient admissions, and ED visits. Veteran-reported health outcomes, including subjective ratings of health.

Exploratory outcomes: Veteran-reported consumption of fruits and vegetables, nutrition security, depression symptoms, and other well-being indices.

We will also assess implementation processes and outcomes.

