### VA FCPRx program

#### Produce prescription benefit

The produce prescription benefit is provided by the non-profit organization About Fresh^© ^ [42]. Enrolled Veterans receive a pre-paid card with a monthly allowance of $100 for 12 months, which can be used at participating grocery stores to purchase fresh fruits and vegetables. Each month’s prescription benefit must be used during the month of issuance and does not “roll over” into subsequent months. Participating Veterans receive a combination of live phone and text support from About Fresh for any challenges with card usage. Participating grocery stores include large, national, and locally based stores throughout Texas, Utah, and surrounding states, such as Albertson’s, Kroger/Smith’s, and Wal-Mart [43].

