#### Culinary education

Along with the monetary benefit of the program, participants will receive education designed to help them integrate the purchased produce into their diet, with a participant choice of: (1) a supportive nutrition class delivered in VA called Healthy Teaching Kitchen, offered virtually once per week for 4 weeks or (2) one-on-one consultation with a VA dietitian.

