### Outcome variables

#### Outcomes

Our primary outcomes will be clinical measures captured in the VA electronic health record, including BMI (constructed from height and weight values) and blood pressure readings (systolic and diastolic), which will be obtained from the Vital Status table in the VA Corporate Data Warehouse (CDW). In addition, HbA1c will be obtained from CDW laboratory data. A power analysis revealed that our planned sample will result in minimal detectable differences for HbA1c of 0.6 mmol/mol, for systolic blood pressure of 6.5 mm and 3.5 Hg for diastolic blood pressure, and 2.4 in BMI units (weight pounds x height inches) × 703).

We will construct healthcare cost variables from VA Managerial Cost Accounting datasets, which is an activity-based cost accounting system that maps VHA resource expenditures to individual patient encounters. Healthcare costs will be captured separately for outpatient, inpatient, emergency department, and pharmacy services. We will sum these costs for healthcare encounters occurring over the follow-up period and adjust for inflation to 2025 US dollars. Similarly, healthcare utilization will be calculated as the number of outpatient and emergency department visits, prescriptions, and inpatient days. These will serve as important secondary outcomes.

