### Limitations

It is important to acknowledge the limitations of VA FCPRx. Because eligibility screening data are EHR-based, we will not have results from Veterans who do not use VA care regularly. The comparison group will meet eligibility criteria but did not enroll in the program for a variety of reasons. This design choice was made to accommodate the clinical embedding approach and to offer the intervention to as many eligible Veterans experiencing food insecurity as possible during an enrollment period. However, because of the inherent differences in patients who do and do not enroll in the program, our estimated effects of the program on patient outcomes will be subject to confounding bias. Our IPTW approach should minimize the impact of measured confounders, but unmeasured confounders may still be present. Therefore, other designs (e.g., cluster randomization) may be important to examine in future work. There may be a high non-response rate for the survey, particularly in the comparison group, and all analyses will report the response rate and details of enrollment procedures. We will report characteristics of both study sites, including the number of VA nutritionists and social workers supported by the site, and we know that participating sites do not have parallel levels of support. Culinary education is offered as part of VA programming and there were no study resources assigned to this programming which may impact the effectiveness of this support. Furthermore, comparison group participants are eligible for this VA benefit and may also participate in culinary education if interested.

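### Outpatient visits and outpatient cost carry no stated exclusion for the program's own VA-delivered education, so the program may raise its own secondary outcomes

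*Protocol article*

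**What the plan says.** All references are to the protocol article.

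- **Cost (Outcomes).** Costs come from an accounting system that assigns VHA spending to patient encounters. They are held separately for outpatient, inpatient, emergency and pharmacy care. Then: "We will sum these costs for healthcare encounters occurring over the follow-up period and adjust for inflation to 2025 US dollars".
- **Utilization (Outcomes).** "healthcare utilization will be calculated as the number of outpatient and emergency department visits, prescriptions, and inpatient days".
- **Utilization (Study design).** The secondary outcomes are listed differently: "Healthcare utilization, including primary care visits, pharmacy utilization, inpatient admissions, and ED visits".
- **Education (Culinary education).** Participants choose "a supportive nutrition class delivered in VA called Healthy Teaching Kitchen, offered virtually once per week for 4 weeks" or a one-to-one consultation with a VA dietitian.
- **Who resources it (Limitations).** "Culinary education is offered as part of VA programming and there were no study resources assigned to this programming". The same section says that comparison Veterans are eligible for this education.
- **Start of follow-up (Data analysis).** The enrolled group's index date is program enrollment. The comparison group's is the first date in the enrollment window on which the Veteran was on the roster and screened positive.
- **Sub-analysis (Data analysis).** Enrollees are compared on outcomes by class attendance: none, some, or all four.
- **Card (Produce prescription benefit).** "The produce prescription benefit is provided by the non-profit organization" that runs the card scheme. "Enrolled Veterans receive a pre-paid card with a monthly allowance of $100 for 12 months", and each month's "benefit must be used during the month of issuance".

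**The concern.** A utilization outcome should measure what the program does to other care. Here part of the program is itself VA care, delivered inside the follow-up window, and the visible text does not separate the two. An enrollee who takes up the education could show more outpatient visits and higher outpatient cost simply because the program was delivered. A real fall in other outpatient use could be masked, or a rise reported that is only the program itself.

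The attendance sub-analysis is the sharpest case. If it uses utilization or cost, the variable that defines the groups is also added into the outcome.

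The two lists of utilization measures make this harder to settle. Classes and dietitian visits would probably not count as primary care visits, but would probably count as outpatient visits.

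**Working it through.** The article gives no sample size, power, background visit rate or education uptake for the cost and utilization outcomes, so there is no figure of the plan's own to reproduce. What follows is a range on stated assumptions.

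**Inputs from the article.** Program encounters: 4 classes (Culinary education), or a consultation, whose number is not given and is taken here as 1. Card: $100 a month for 12 months. Intervention group: 500.

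**Assumptions.** Background outpatient visits of 10 or 20 a year; between-group difference in education uptake of 25% to 100%; cost per encounter of $50 to $300; every class or consultation recorded as one outpatient encounter; no effect on other care.

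**Main contrast, 12 months.** Added visits per enrollee = encounters × uptake difference. The smallest value is 1 × 0.25 = 0.25 and the largest is 4 × 1.00 = 4. Rate ratio = (background + added) / background.

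| Background visits | 1 encounter, 25% | 4 encounters, 50% | 4 encounters, 100% |
|---|---|---|---|
| 10 | 10.25/10 = 1.03 | 12/10 = 1.20 | 14/10 = 1.40 |
| 20 | 20.25/20 = 1.01 | 22/20 = 1.10 | 24/20 = 1.20 |

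**Main contrast, 6 months.** The same encounters sit on a smaller base. With 6 background visits, four classes and a 50% uptake difference give 8/6 = 1.33.

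**Outpatient cost.** Added cost = unit cost × added visits: from $50 × 0.25 = $12.50 to $300 × 4 = $1,200 per enrollee.

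**Would a test notice?** Assume 500 per group, unweighted, and a negative binomial model with dispersion d. The standard error of the log rate ratio is √[(1/m₁ + d)/500 + (1/m₂ + d)/500]. The chance of declaring an increase at two-sided 0.05 is Φ(log(m₂/m₁)/SE − 1.96).

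- 10 against 12 visits: 0.96 (d = 0.5) and 0.79 (d = 1.0).
- 20 against 20.5 visits: 0.08 (d = 0.5) and 0.06 (d = 1.0).

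**Attendance sub-analysis.** With 12 background visits a year, all four classes against none gives (12 + 4)/12 = 1.33 at 12 months and (6 + 4)/6 = 1.67 at 6 months, with no effect on other care. Comparison-group uptake does not enter this contrast.

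**Card.** $100 × 12 = $1,200 per enrollee at most, or $1,200 × 500 = $600,000 in all. Unused money lapses each month, so at an assumed 25%, 50% or 75% use the figure is $300, $600 or $900 per enrollee.

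**The case against.** The article neither includes nor excludes the education by name. Which encounter types count as outpatient visits is a detail that an article may leave to the full protocol, and Table 2, which is said to hold the metrics and analytic approach, is not visible. This stands as a limit on certainty: that the contacts are recorded as outpatient encounters is an inference, though the natural one.

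Comparison Veterans may take the same education, and any Veteran who screens positive is referred to a social worker or dietitian. The index dates can also push the other way, because comparators are followed from the positive screen while enrollees are followed from enrollment, which comes after that referral. This also stands: only the net difference enters the main contrast, and neither its size nor its sign is fixed by the text. It does not help the attendance sub-analysis.

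Counting VA-resourced education in total VA outpatient cost is a legitimate payer view, and removing dietitian visits could delete real care that the program changes. That argues against mandatory exclusion, but not against reporting both versions.

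The Study design list is open-ended, so the Outcomes section may broaden it rather than contradict it. Even so, admissions and inpatient days are different measures, as are primary care visits and all outpatient visits.

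A reader might also infer that leaving out the card makes the cost comparison wrong. The article does not support that. The outcome is named healthcare cost, the card comes from an outside non-profit, and no cost-effectiveness or net-cost analysis is described. The abstract says only that results will inform the design of cost-effective programs. The omission matters only if the result is read as net program cost.

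**Conclusion.** The point holds as a gap in the definition of two secondary outcomes, outpatient visits and outpatient VA cost. Nothing visible keeps the program's own education out of them. If it is recorded as outpatient care, it raises them by the difference in uptake between the groups.

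The size is unknown: on the assumptions shown, from negligible (rate ratio 1.01) to large (1.40) at 12 months. The attendance sub-analysis is affected directly if it uses utilization or cost.

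The reading that the program must inflate its own outcome goes too far, because comparators have access to the same education and the recording is inferred. Inpatient, emergency and pharmacy outcomes are not directly affected, nor are the primary clinical outcomes. For the card, $1,200 is a ceiling rather than the expected spend, and leaving it out is consistent with the outcome's name.

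**What to change.** 1. Reconcile Study design with Outcomes on the named utilization measures: primary care visits or all outpatient visits, and admissions or inpatient days.
2. Report outpatient visits and outpatient cost both with and without program-type education encounters (Healthy Teaching Kitchen classes and program-type dietitian consultations), using one definition for both groups.
3. Use the version without these encounters wherever the class-attendance comparison uses utilization or cost.
4. Label the cost outcome as VA healthcare cost excluding the produce card. Add the card dollars actually used, which the Data management section says are already transferred to the study team, before making any net-cost or cost-saving statement.

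The cost is some wording, an encounter-type filter and a second run of the outpatient models; no new data collection is needed. The version without education will also drop some nutrition visits unrelated to the program, which is why both versions should be shown.

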#### Implementation metrics

Implementation processes include an interview approach based on the RE-AIM framework to assess implementation processes and experiences by site to understand adaptation. We will also assess implementation strategies by recording field notes and conducting brief inquiries with implementation staff. Implementation outcomes are measured by characteristics, implementation program data (e.g., site capacity by FTE for staff, and number of nutritionists and dietitians per qualifying Veteran by site).

#### Independent variables

To reduce the influence of confounding variables on our estimates, we will consider a number of measurable patient characteristics in our analyses. Demographic characteristics will include age, race, gender, marital status, priority group, insurance status, and rurality. Clinical characteristics will include the Charlson comorbidity index and the presence of mental health diagnoses. Additional information about clinical metrics and additional measures is shown in Table 2.

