### Eligibility and screening

Eligible participants are identified using VA EHR data from among currently active patients defined by a visit to a participating VA medical center within the preceding 12 months. Inclusion criteria are:

1) An indicator in the VA EHR for economic hardship (Designated membership in VA benefits criteria priority groups 5 or 7, based on Veteran benefits. These groups indicate a Veteran who has low-income without a service-connected disability).

2) One or more diet-sensitive cardiometabolic condition a) hypertension, b) obesity, or c) type 2 diabetes or malnutrition related diabetes. Cardiometabolic condition is determined by diagnostic code within the VA EHR (International Classification of Disease, ICD-10) or by laboratory values. Table 1 shows the specific EHR ICD-10 codes and laboratory values. Consent is not required for this screening or identification process.

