#### Comparison group participants

The comparison group for our study will consist of Veterans who meet eligibility criteria at study sites (e.g., screening and cardiometabolic conditions) but did not participate in the intervention. It is anticipated that this group will be enrolled after the intervention group has reached capacity. This comparison group was chosen based on likely demographic similarity and the study goal for a pragmatic rather than a randomized design focus on a program embedded in VA clinical care. There are multiple potential reasons Veterans might qualify for inclusion but not enroll in VAFCPRx, including not being offered enrollment by clinical staff during the pragmatic clinic enrollment process or because they decline to participate.

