### Data analysis

At baseline, descriptive analyses of participants and the comparison group will assess any group differences in their characteristics (implementation or comparison), diet-sensitive condition, location site, age, military branch, and race/ethnicity. The index date for the treatment group will be the date of enrollment in the VA FCPRx program, while the index date for the comparison group will be the first date during our enrollment window in which the Veteran was listed on the eligibility roster and screened positive for food insecurity. We will construct propensity scores for program enrollment using multivariable logistic models including the independent variables listed above and use these propensity scores to conduct inverse probability treatment weighting (IPTW) analyses to compare outcomes between individuals in the FCPRx group and the comparison group. For each of these variables, our primary measure will be the value most proximal within a 2-month window surrounding the follow-up time period (i.e., 6 and 12 months). In secondary analyses, we will calculate averages for individuals with multiple values. In addition, our primary analyses will carry forward baseline values for individuals with missing values in the follow-up period. In exploratory analyses, we will include only those with non-missing outcome values.

In our primary analysis, we will assess differences in clinical measures, including body mass index (BMI), systolic blood pressure (SBP), diastolic BP (DBP), A1c, and self-reported health between patients in the treatment and comparison groups. For each outcome of interest, we will use a linear model with an ITPW approach to estimate the treatment effect and ensure the balance of baseline covariates, including baseline clinical measures. As a secondary analysis, we will compare within-person changes in clinical measures between the two groups.

Secondary outcomes include healthcare cost and utilization, and self-rated health. Exploratory outcomes include fruit and vegetable consumption, nutrition security, depression symptoms, and well-being indices. We will assess changes in secondary and exploratory outcome measures for those participants with both baseline and follow-up values. We will use generalized linear models and two-part models for healthcare cost outcomes and Poisson or negative binomial models for healthcare utilization outcomes. All comparisons will be performed at both 6- and 12-month follow-up intervals.

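### The propensity model as described names no index-date drug treatment, so baseline prescribing can confound the BMI, blood pressure and HbA1c comparisons

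*Protocol article*

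**What the plan says.** The Study design section defines the primary outcomes as "Clinical measures, including body mass index (BMI), blood pressure, and metabolic control (HbA1c) derived from the VA EHR". Eligible Veterans have "One or more diet-sensitive cardiometabolic condition a) hypertension, b) obesity, or c) type 2 diabetes or malnutrition related diabetes", and the eligibility text contains no medication criterion. The comparison group meets the same criteria "but did not participate in the intervention", either because staff did not offer the program or because the Veteran declined.

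The Independent variables section lists demographic characteristics and then says "Clinical characteristics will include the Charlson comorbidity index and the presence of mental health diagnoses". It closes with a pointer: "Additional information about clinical metrics and additional measures is shown in Table 2". The Data analysis section constructs the propensity score with "multivariable logistic models including the independent variables listed above". It continues: "For each outcome of interest, we will use a linear model with an ITPW approach to estimate the treatment effect", and says that the weighting is to balance baseline covariates, baseline clinical measures among them.

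Drug data appear in the Outcomes section as two secondary outcomes: a number of prescriptions, within utilization, and a pharmacy cost, within costs. Both are totals over all drugs, and neither is described as part of the primary model.

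**The concern.** Weighting can remove only confounding by variables that are in the propensity model. Antihypertensive, glucose-lowering and weight-loss drugs act directly on the measures that the Outcomes section takes as primary, "clinical measures captured in the VA electronic health record, including BMI (constructed from height and weight values) and blood pressure readings" and HbA1c. Enrollment depends on who is offered the program and who accepts, and nothing in the design makes drug treatment at the index date equal between groups.

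The planned balance on baseline readings helps but is not a substitute. Two Veterans with the same index blood pressure, one on several drugs and one on none, differ in underlying severity, in contact with care and in expected course over 12 months. If the mix of such Veterans differs by group after weighting, part of the difference at 6 and 12 months reflects baseline treatment and not the produce benefit. The error can go in either direction, and a larger sample does not reduce it.

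**Working it through.** **1. Which variables are named where**

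| Place in the protocol article | What is named | Drug class at index? |
|---|---|---|
| Independent variables | Age, race, gender, marital status, priority group, insurance, rurality; Charlson index; mental health diagnoses | No |
| Data analysis | Propensity score from the list above; balance on baseline clinical measures | No |
| Outcomes | Number of prescriptions; pharmacy cost (both secondary outcomes) | No, totals only |
| Limitations | Unmeasured confounding in general | Not mentioned |
| Table 2 | Content not shown | Cannot be judged |

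The readable text therefore states an adjustment set, and index-date drug treatment is not in it.

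**2. The plan's own yardstick**

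The Outcomes section gives minimal detectable differences of 6.5 mmHg for systolic pressure, 3.5 mmHg for diastolic pressure, 2.4 BMI units, and 0.6 for HbA1c, printed in mmol/mol. These cannot be reproduced, because the article gives no significance level, power, standard deviations or comparison-group size for the record-based outcomes. Only an implied standard deviation can be found. Assuming two-sided 5% and 80% power, SD = MDD / [(1.960 + 0.842) × √(2/n)]. For systolic pressure this gives 36.7 mmHg at n = 500 per group and 25.9 mmHg at n = 250. The point does not turn on these figures; 6.5 mmHg serves only as a scale.

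**3. Size of the confounding, by assumption**

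Bias = (residual difference between groups in the proportion on the drug class) × (difference in expected follow-up reading associated with that class). The documents give neither input. Assumed: 5 to 10 percentage points, and 6 to 10 mmHg systolic, 2 to 4 BMI units, 0.7 to 1.5 HbA1c percentage points.

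- Systolic: 0.05 × 6 = 0.3 to 0.10 × 10 = 1.0 mmHg. Against 6.5: 0.3/6.5 = 4.6% to 1.0/6.5 = 15.4%.
- BMI: 0.05 × 2 = 0.1 to 0.10 × 4 = 0.4 units. Against 2.4: 4.2% to 16.7%.
- HbA1c: 0.05 × 0.7 = 0.035 to 0.10 × 1.5 = 0.15 percentage points. If the stated 0.6 means percentage points, this is 6% to 25% of it. If the printed mmol/mol is meant, the share is much larger. The unit is a separate question, so HbA1c is not used to size this point.

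Because the baseline reading is also to be balanced, the relevant second factor is the difference in follow-up reading *at equal index reading*. That may be smaller than a full drug effect, so these figures are illustrations and not estimates.

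**4. Effect on the test**

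With SE = 6.5/2.802 = 2.32 mmHg (two-sided 5%, 80% power assumed) and no true program effect, a bias of 0.3 mmHg raises the rejection rate from 5% to 5.2%, and 1.0 mmHg raises it to 7.2%. A wider assumption of a 30 point difference and a 10 mmHg effect gives 3.0 mmHg, 46% of 6.5, and a rejection rate of 25%.

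**The case against.** Four objections deserve weight.

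- **Table 2 is not shown.** The Independent variables section refers to it for further clinical metrics, so a drug variable there cannot be excluded. This stands and makes the point conditional. The article introduces the table as an overview of PRISM/RE-AIM metrics, measurement and analytic approach, not as the covariate list for the propensity score.
- **The list need not be closed, and an article condenses.** This stands in part: drug-class definitions belong in a fuller document. But the article names its adjustment variables and ties the propensity model to them, so it is fair to say that this list omits a direct determinant of the primary outcomes.
- **Baseline readings are balanced, within-person change is a secondary analysis, and the Limitations section concedes unmeasured confounding.** The first two remove part of the confounding. The third does not answer the point, because the study already uses VA prescription data and this confounder can be measured.
- **Engagement with care may differ less than it seems.** Comparators are indexed at a positive food-insecurity screen, which also leads to referral to a social worker or dietitian, and they may use the same culinary education. This stands: the direction and size of any imbalance are unknown.

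A reader might go further and infer that drug changes after the index date bias the primary result, or that drug data enter the plan only as a prescription count. The documents support neither. Everyone who enrolled is analyzed as enrolled whatever benefit they used, so prescribing changes that follow enrollment may be part of the program's total effect. Pharmacy cost is captured as well as the count.

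**Conclusion.** The point holds for baseline treatment. As described, the propensity model leaves out drug use at the index date, a measurable determinant of BMI, blood pressure and HbA1c, in a comparison where allocation is not controlled. It is a worthwhile and cheap improvement and does not invalidate the design. It is conditional on Table 2 not already naming such variables.

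The size is not known. Under the narrower assumptions above, the systolic shift is about 5% to 15% of the stated detectable difference and the false rejection rate barely moves; much larger imbalances would be needed for a serious effect on the test. It is also tempting to express the shift as a share of a small true program effect, which makes it look larger, but the documents give no such effect.

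**What to change.** Unless Table 2 already provides for it:

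1. Add index-date indicators to the propensity model for antihypertensive use, glucose-lowering use (insulin separately) and weight-loss drug use, taken from VA pharmacy data. Report their balance between groups before and after weighting.
2. As description only, tabulate by group the class-specific starts, intensifications and reductions between index and 6 and 12 months, beside the corresponding primary outcome. Neither adjust for these changes nor restrict the analysis to Veterans without them: they may be consequences of the program, and conditioning on them can introduce selection bias.

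The cost is coding of drug classes from data of a kind the study already uses, one additional descriptive table, and slightly more variable weights.
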